### Timeline

The study will span approximately 15 months (Table 1). The first 3 months will be the preparation phase. A crowdsourcing open call will be promoted and held to generate an initial crowdsourced intervention 1.0. Interventions 2.0, 3.0, 4.0 will be developed during the trial with inputs from the ongoing open call. The following 12 months will be the intervention phase. The intervention will be sequentially rolled out in each of the four clusters following the stepped-wedge design. Participants will be surveyed at baseline and every 3 months thereafter. By the 15th month, all participants will have received the intervention for a 3-month interval and the final follow-up survey will be conducted. The SESH research group will manage and oversee intervention progression.

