## Methods/design

### Study design and rationale

This pragmatic stepped-wedge cluster randomized trial is a sub-study of a multi-center demonstration of PrEP engagement and initiation among at-risk populations in two Chinese provinces, Hubei and Guangdong. (Study ID: CO-US-276-5866) In the demonstration, participants recruited from both sites will be provided with daily oral PrEP for 12 months with quarterly follow-up visits (questionnaires and clinical assessments). Participants are encouraged to adhere to daily regimen throughout the study. At enrollment, every participant will be given access to a WeChat-based PrEP education mini-app that has been pilot tested and refined in a previous study project among Chinese GBMSM [25]. Among the participants who successfully initiate PrEP through the study, the first 700 participants from both sites will be included in the stepped-wedge trial.

This stepped-wedge design will be a four-phased implementation organized into four clusters with each cluster starting the intervention at three-month intervals, so that by the end of the 12-month study period all clusters will receive the intervention. (Table 1) A pragmatic trial is aligned with the aim of our study as we are interested in examining the crowdsourced intervention in a real-world context rather than strictly measuring its efficacy in an ideal setting [26]. This stepped-wedge design allows the evaluation of the intervention’s external validity and informs public health decisions to promote PrEP adherence in at-risk populations [27].

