**Table 1 Tab1:**
[figure not shown]
Stepped-wedge design of a crowdsourced intervention for facilitating PrEP adherence in at-risk populations in China

In this closed cohort stepped-wedge design, all participants will be identified at the onset of the trial. All participants will be engaged with the intervention or control condition at different crossover points. Minimal implementation lag will be expected as the predesigned interventions consist of social media components and immediately start and finish [22]. The control condition includes routine follow-up visits (surveys and clinical assessments) by community-based organizations and local hospitals following the setup of the demonstration study. The intervention condition includes a crowdsourced intervention to facilitate PrEP adherence.

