### Cluster randomization

Block randomization will be used to control for potential secular trends and bias related to the imbalance in cluster-level covariates [30]. Block size will be eight. Participants at each site will be assigned to blocks based on the timing of PrEP initiation. Participants enrolled at the same site will be grouped to the same block. Blocks will be assigned to the four clusters using a computer-generated randomization list that is generated by a study staff member.

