### Intervention condition - receiving the intervention materials

Participants will be assigned into four clusters in blocks at each site. All clusters will receive the intervention initiated at a different time. Updated interventions 2.0, 3.0, 4.0 will be implemented for clusters b, c, d, respectively, in addition to cluster a receiving intervention 1.0. Each cluster will receive the intervention for 3 months over a 12-month period. The first intervention will start 2 weeks after the baseline recruitment. The time intervals of the crowdsourced intervention are aligned with the follow-up intervals in the PrEP Demo study. That is, the first cluster will receive their first intervention 2 weeks after they fill out the baseline survey, and the second, third, and fourth cluster will receive their first intervention 2 weeks after they complete the follow-up surveys at 3, 6, 9 months respectively. The intervention will be delivered to each cluster biweekly in the 3-month intervention period by the CBOs. CBO peer educators or volunteers will contact participants via WeChat and implement the intervention each time.

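### The 15-month timeline and the cohort fixed at trial start leave no time for recruitment, although participants enrol as they initiate PrEP and are followed on their own clocks

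*Protocol article*

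**What the plan says.** The protocol article describes the trial calendar in two ways.

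**A common start and a fixed end.** Under Study design and rationale: "In this closed cohort stepped-wedge design, all participants will be identified at the onset of the trial". Under Timeline: "The first 3 months will be the preparation phase" and "The following 12 months will be the intervention phase". The same section concludes: "By the 15th month, all participants will have received the intervention for a 3-month interval and the final follow-up survey will be conducted". The preparation phase is described there only as the open call that yields intervention 1.0.

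**Enrolment over time, with a clock for each person.**
- Study design and rationale: among those who initiate PrEP in the demonstration study, "the first 700 participants from both sites will be included in the stepped-wedge trial".
- Eligibility: people hear of the trial when they initiate PrEP in hospital.
- Cluster randomization: "Participants at each site will be assigned to blocks based on the timing of PrEP initiation".
- Intervention condition - receiving the intervention materials: "the first cluster will receive their first intervention 2 weeks after they fill out the baseline survey". The other three clusters start 2 weeks after their own surveys at 3, 6 and 9 months, and each cluster receives 3 months of intervention.
- Data collection activities: month 0 is PrEP initiation, and all participants must attend through month 12.
- Trial status: recruitment has begun.

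The text gives no recruitment period. Table 1, cited for the schedule, could not be seen. The Analysis section puts time in the mixed model as a fixed effect, citing possible growth in loss to follow-up, but does not say whether time means calendar step or visit since initiation.

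**The concern.** The two descriptions cannot both hold. If everyone starts together, calendar time and time since initiation are the same, and 15 months is enough. If people enrol as they initiate PrEP, the two clocks separate. The end date then moves later by the length of recruitment, and the model's time term could mean either of two different variables.

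Three things depend on this:
- The duration and the completion claim are misstated for everyone who enrols after the first participant.
- An analyst who follows the common-start description might code time as a calendar step, although intervention status changes with each person's own visit month.
- If month 15 were treated as a hard end, the missing data would be late visits and the missing exposure would fall mainly in the clusters that start last.

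**Working it through.** **Inputs.** Preparation 3 months and intervention phase 12 months (Timeline). Follow-up 12 months from own initiation (Data collection activities). Starts 2 weeks after the baseline, 3-, 6- or 9-month survey, and exposure 3 months (Intervention condition - receiving the intervention materials). Recruitment length r is not stated and is treated as an assumption.

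**Step 1, the plan's own figure.** 3 + 12 = 15 months. It reproduces only with r = 0.

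**Step 2, with recruitment after preparation.** Last month-12 visit = 3 + r + 12 = 15 + r.

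| Assumed r (months) | Last month-12 visit (study month) |
|---|---|
| 0 | 15 |
| 3 | 18 |
| 6 | 21 |
| 12 | 27 |

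**Step 3, the most favourable reading.** Suppose enrolment runs from study month 0, during preparation. The last month-12 visit is then at r + 12: month 15 for r = 3, month 18 for r = 6, month 24 for r = 12. So 15 months suffices only if r is at most 3. This reading also fits the Timeline poorly. The first cluster starts 2 weeks after its own baseline, yet the preparation phase is there to produce the material it receives, and the 12-month intervention phase is placed after it.

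**Step 4, the two clocks.** A person who enters e months after the first enrollee has visit v at study month 3 + e + v. At study month 12, someone with e = 0 is at visit 9 (3 + 0 + 9), someone with e = 3 is at visit 6 (3 + 3 + 6), and someone with e = 6 is at visit 3 (3 + 6 + 3). Whether each is under intervention depends on cluster and v, not on the calendar month. Under the per-person schedule, therefore, the steps of the wedge are defined by v.

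**Step 5, the last cluster's exposure.** Two weeks is 14 / 30.4375 = 0.46 month. Counted from first delivery, the fourth cluster's 3 months end at 9 + 0.46 + 3 = 12.46 months, after its month-12 survey, by which time it has had 3 - 0.46 = 2.54 months. Counted from the 9-month survey, they end at 9 + 3 = 12 and fit. The text does not say which count applies.

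**The case against.** The strongest reply is that the Timeline is only a sketch: preparation plus one participant's schedule, qualified as approximate, with the calendar end moving as accrual requires. Several parts of this stand.

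- **No data cut-off is stated.** A reader might infer that month-12 outcomes and late-cluster exposure will be lost. The article does not support that: it requires every participant's month-12 visit, counted from that person's own initiation. A size for the loss would also need a recruitment length and a hard close, neither of which is given. For illustration, take uniform enrolment closed 12 months after the first entry, with 2 weeks rounded to 0.5 month. The share of the fourth cluster that never starts is then (r - 2.5) / r: 17%, 58% and 72% for r of 3, 6 and 9. Figures so sensitive to an unstated input describe an assumed study, not this plan.
- **Calendar shocks are partly handled by design.** A reader might infer that COVID-19 disruption biases the comparison. But blocks are formed within site by time of initiation and randomised across the clusters, which balances such shocks in expectation. The Cluster randomization section gives control of secular trends as a purpose.
- **The two-week overrun is small and conditional.** It disappears if the interval runs from the survey. If it runs from first delivery, every cluster overruns its next survey by two weeks, not only the fourth.
- **An article may leave accrual dates to the full protocol.** The missing recruitment period is therefore not the fault.

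What the reply does not remove is the statement that all exposure and the final survey are complete by month 15, and that all participants are known at trial start. Reading the timeline as approximate might absorb a few weeks, but not an open-ended recruitment period.

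**Conclusion.** The contradiction is in the text and should be corrected. The common-start and month-15 statements conflict with enrolment at PrEP initiation and with follow-up on each person's own clock. If recruitment follows preparation, the true duration is about 15 + r months, so the stated duration and completion claim are wrong for any r > 0.

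The documents support no estimate of lost outcomes or lost exposure. Such loss would follow only if the 15-month end were enforced, and its size cannot be given because r is unknown. The time term is undefined between two clocks that the design separates. Its stated rationale, growing loss to follow-up, fits time since initiation, so this needs a definition and does not show that the model is wrong. The fourth cluster's overrun is at most about two weeks and depends on how the interval is counted.

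**What to change.** 1. **Timeline:** state that the study ends when the last enrolled participant completes the month-12 visit (3 months of preparation + recruitment period + 12 months), and give the recruitment period.
2. **Study design and rationale:** replace the sentence that places identification of all participants at trial start. Describe a cohort closed on participant time: recruitment is continuous, each person is followed from month 0 to month 12, and nobody joins at a later step.
3. **Analysis:** state that the model's time effect is the scheduled visit since PrEP initiation (3, 6, 9, 12 months). Add site and calendar period of initiation as fixed effects, because blocks are formed on these two factors.
4. **Intervention condition and Timeline:** reconcile whether the 3-month intervention interval is counted from the survey or from first delivery two weeks later, and how that relates to the month-12 survey.

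The cost is wording, a few model terms and a later stated end date. No extra participants or visits are needed, because each person is already due 12 months of follow-up.

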### Data collection activities

In accordance with the demonstration study design, participants in the stepped-wedge design will undergo clinical monitoring for assessment of adherence and side effects every month for the first 3 months after PrEP initiation and every 3 months starting from the 4th month per current US CDC and WHO guidelines, provided by their respective study hospital. All study participants will be required to complete clinical visits at their respective study hospital for PrEP initiation (month 0) as well as for follow-up at months 1, 2, 3, 6, 9 and 12 (Table 1). Baseline survey and follow-up surveys will be administrated through a professional Chinese online survey engine Sojump (Sojump, Shanghai, China) that has been widely used in China-based research studies. Research staff will monitor the survey responses and upload to a secure Dropbox account on a weekly basis.

### Follow-up plan

During study planning in the first half of 2020, reports have emerged regarding the adverse impact of the COVID-19 pandemic on sexual health for people at risk of HIV, including fewer HIV tests, STI screens and less consistent PrEP refills. We have included questions related to the impact of COVID-19 on sexual behaviors and PrEP readiness to our screening survey, and we will monitor accrual and adherence to clinic visits and PrEP with additional caution. As needed, we will incorporate changes in the protocol as required by local pandemic patterns in Hubei and Guangdong provinces.

### Data management

All data from baseline and follow-up surveys are anonymous and are submitted directly into computers and transmitted securely using SSL (TLS) 128-bit encryption. Data will be located password-protected on Sojump and will only be accessed by research group members. Data can be readily downloaded and converted to the format of commercially available statistical software. Survey responses will be kept separately from participants’ contact information; the two files will be linked with a non-descript identifier that is encrypted and password-protected. An independent external advisory committee consisting of STI experts has been formed. The committee will meet periodically to review and evaluate data collection and study progress.

### Analysis

The primary outcome will be evaluated at the end line. We will examine a hypothesis that a crowdsourced intervention can facilitate PrEP adherence. As this is a binary outcome with a small number of clusters, we will use generalized linear mixed models (GLMM) for the primary outcome analysis [31]. It is appropriate to assume that the intervention effect is common across clusters as the intervention will be implemented to all clusters directly by CBO staff. The model will include intervention status and time as fixed effects given the potentially increasing loss-to-follow-up. The estimated intervention effects will be reported with 95%CIs and *p* values.

All secondary outcomes will be binary (continuous variables will be categorized into binary variables). Similar analysis will be conducted for secondary outcomes including proportion of people who test for HIV in the past 3 months, proportion of mhealth use, proportion of people who feel confident in their self-efficacy, and HIV incidence. Descriptive data will be used to summarize clusters.

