Each follow-up at the 3, 6, 9, 12 months will include an online survey and a clinical assessment. (Table 1) The online survey will collect data related to number of sexual partners, HIV testing, PrEP uptake (missing doses in the past 90, 30, 7 days for daily PrEP users vs. number of sex and number of doses taken in the past 90, 30 days for on-demand PrEP users), engaging in WeChat mini-app, and evaluation of crowdsourced PrEP adherence intervention. Participants will be assessed on their PrEP attitudes, PrEP stigma, PrEP use self-efficacy, HIV-related anxiety, social support and overall perceived stress using validated scales at 6 and 12 months. For all follow-ups, transgender participants will additionally respond to questions related to whether they are currently using gender affirming hormones, and if they were, whether they are concerned about drug-drug interaction and whether they have mentioned taking hormones to the doctors who are prescribing PrEP. The clinical assessment will include testing results related to HIV, STIs (syphilis, HBV, HCV), standard blood test, standard urine test, liver function test, and renal function test. If a participant seroconverts to HIV positive, their participation in the study will be terminated and they will be referred to their local provider or health department for antiretroviral therapy. Otherwise, participants will be prescribed TDF-FTC for another 3 months after each follow-up at 3, 6, 9 months.

The primary outcomes of this sub-study are PrEP adherence and retention in PrEP care throughout the study period. PrEP adherence will be measured by self-report in quarterly behavioral assessment surveys and pill count at clinical follow-ups among a subset (a total of 120 participants who initiate PrEP during the study in Guangdong will be sampled to receive pill count using systematic random sampling). Retention in PrEP care will be measured via self-initiated or physician-advised PrEP discontinuation, PrEP re-initiation, and self-initiated switch rates from once daily and on-demand regimens. Details about the study measures are illustrated in Table 2. Optimal daily PrEP adherence will be considered to be 6–7 pills weekly. Optimal adherence to an on-demand regimen will be defined as having two pills at least 2 h before each sexual encounter, followed by one pill 24 hours after the first dose and one pill after the second dose.

**Table 2 Tab2:** Outcome measures and timepoints of data collection

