**Secondary outcomes**		
**HIV testing**	Frequency of participants, defined as the number of participants who reported being tested for HIV during the previous three months	3, 6, 9, 12 months
**Sexual and mental health mini-app use**	Frequency of participants, defined as the number of participants who reported using the mini-app in the past three months to receive information about sexual and mental health comparing their pre-intervention and post-intervention engagement	3, 6, 9, 12 months
**PrEP self-efficacy**	Frequency of participants, defined as number of participants who had an increase in PrEP self-efficacy when comparing their pre-intervention and post-intervention self-efficacy	3, 6, 9, 12 months
**HIV incidence**	Frequency of participants, defined as number of participants who reported who have newly diagnosed with HIV in the previous three months	3, 6, 9, 12 months

Secondary outcomes will include HIV testing rate, mHealth use, self-efficacy assessment, and HIV incidence.

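### PrEP self-efficacy, the one scale among the secondary outcomes, has two definitions and two schedules, and is dichotomised by rule

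*Protocol article*

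**What the plan says.** The protocol describes self-efficacy in four places.

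- **Study measures and outcomes, baseline survey:** PrEP use self-efficacy is collected at baseline.
- **Study measures and outcomes, follow-up:** self-efficacy belongs to a group of scales measured "using validated scales at 6 and 12 months".
- **Table 2, secondary outcomes:** the endpoint is the "number of participants who had an increase in PrEP self-efficacy when comparing their pre-intervention and post-intervention self-efficacy", with data collection at 3, 6, 9 and 12 months.
- **Analysis:** the endpoint is the "proportion of people who feel confident in their self-efficacy".

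On method, the Analysis section says "Similar analysis will be conducted for secondary outcomes". The primary analysis it points to is a generalised linear mixed model (GLMM), of which it says "The model will include intervention status and time as fixed effects". The same section sets a rule for the form of these outcomes: "All secondary outcomes will be binary (continuous variables will be categorized into binary variables".

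The text under Table 2 lists four outcomes: "Secondary outcomes will include HIV testing rate, mHealth use, self-efficacy assessment, and HIV incidence". Table 2 words mini-app use, like self-efficacy, as a comparison of engagement before and after the intervention.

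**The concern.** A rise from before to after the intervention and a level of confidence are different endpoints and can give different answers. With both in the protocol, the choice could be made after the data are seen.

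The Table 2 version also does not suit the design. Every participant crosses over once, so a pre-to-post rise yields one yes/no value per person. No matching value from a control period is defined. Any drift over the year on PrEP, and measurement noise, would count towards success.

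The schedule conflict decides whether values exist on both sides of each cluster's intervention quarter, and how precisely the effect can be estimated.

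Dichotomising is a stated rule, not a detail left open, and it discards information from a score already being collected.

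**Working it through.** **The plan's own figure.** The protocol gives no power figure for secondary outcomes. Its one calculation, for the primary outcome, can be reproduced and fixes the variance model used below. The Hussey and Hughes model with 4 clusters, 5 measurement times, ICC 0.02, variance 0.4 × 0.6 = 0.24, difference 0.2 and two-sided alpha 0.05 needs 27 per cluster-period (power 0.813; 26 gives 0.7997). Then 27 × 4 × 5 = 540, the stated total. This point does not dispute that figure.

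**Which endpoint fits the model.** The model needs a value for each participant at each visit, with intervention status changing between visits. Feeling confident at a visit is such a value. A rise from pre to post is not: at month 3 it can exist only for cluster a, and for cluster d only at month 12, and no unexposed participant ever has one.

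**How much noise counts as a rise.** If the change score is symmetric, continuous and free of ties, half of participants rise with no effect at all. A drift of 0.2 SD of the change score makes it 58%, and 0.5 SD makes it 69%. Ties on a coarse scale lower these shares.

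**Timing.** The Intervention condition section starts clusters a to d two weeks after the baseline, 3-, 6- and 9-month surveys, each for three months. With the scale at 0, 6 and 12 months:

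| Cluster | Intervention quarter | Last value before | First value after |
|---|---|---|---|
| a | 0–3 | month 0, adjacent | month 6, 3 months late |
| b | 3–6 | month 0, 3 months early | month 6, adjacent |
| c | 6–9 | month 6, adjacent | month 12, 3 months late |
| d | 9–12 | month 6, 3 months early | month 12, adjacent |

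No cluster has adjacent values on both sides.

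**Precision of the two schedules.** A version that can be checked by hand treats cluster and time as fixed. The variance of the effect is then proportional to 1/S, where S = Σx² − Σ(cluster total)²/T − Σ(time total)²/4 + (grand total)²/(4T). Here x is 1 when exposed and T is the number of measurement times, baseline included.

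- Former recipients coded as still exposed. Quarterly: 10 − 30/5 − 30/4 + 100/20 = 1.50. At 0/6/12: 6 − 10/3 − 20/4 + 36/12 = 0.667. Ratio 2.25.
- Former recipients coded as back in control. Quarterly: 4 − 4/5 − 4/4 + 16/20 = 3.00. At 0/6/12: 2 − 2/3 − 2/4 + 4/12 = 1.167. Ratio 2.57.

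With random cluster effects, ICC 0.02, 135 or 175 per cluster, and within-person correlation of 0 or 0.5, the ratios are 2.23 to 2.24 and 2.49 to 2.54. They do not depend on the score's SD.

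**Cost of dichotomising.** Assume a normal score and a simple two-group comparison. With a proportion p on one side of cut c, relative efficiency is φ(c)²/[p(1 − p)].

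| p | Efficiency | Sample size multiplier | Power, if 80% when continuous |
|---|---|---|---|
| 0.5 | 0.1592/0.25 = 0.64 | 1.57 | 61% |
| 0.7 | 0.58 | 1.74 | 57% |
| 0.8 | 0.49 | 2.04 | 50% |
| 0.9 | 0.0308/0.09 = 0.34 | 2.92 | 37% |

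**Mini-app use.** Table 2 collects it at 3, 6, 9 and 12 months, each time about the past three months. The Control condition section introduces the app at recruitment. Cluster a starts its intervention two weeks after baseline, so its first reported quarter is already its intervention quarter and it has no earlier one to compare.

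**The case against.** The strongest reply is that the Analysis section already provides a controlled comparison. It puts the proportion who feel confident, which is a level, through a model with intervention status and time. That stands. A reader of Table 2 alone might infer that self-efficacy will be reported as an uncontrolled before-after result. The documents do not support this, because they never say that the Table 2 rise overrides the Analysis section. What remains is that the two sections name different endpoints and only one fits the model.

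Two other inferences also go too far.

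- The blanket rule might suggest that several outcomes lose information. HIV testing, mini-app use and HIV incidence are yes/no by definition. The other scales in the follow-up survey, "HIV-related anxiety, social support and overall perceived stress using validated scales at 6 and 12 months", are not listed as secondary outcomes.
- The 6- and 12-month schedule might seem to leave month 6 as the only controlled comparison. That holds only if former recipients count as still exposed. The Control condition section puts clusters outside their intervention period in the control condition, and on that coding month 12 compares d with a, b and c. The sparse schedule costs precision and adjacent values, but a controlled comparison survives.

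It is also fair that a cut-point may properly sit in the SAP, so its absence is not criticised here, and that the efficiency figures rest on an assumed distribution. Choosing a binary summary can be defended for ease of reading. That supports showing one alongside the score, not replacing the score with it.

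**Conclusion.** The point holds for one secondary outcome. Self-efficacy has two incompatible definitions and two incompatible schedules, and a rule turns its score into a yes/no variable without a stated reason. The pre-to-post rise cannot be analysed in the planned model; the confidence level can.

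The schedule matters by a factor of about 2.2 (exposure persists) to 2.5 (return to control) in the variance of the effect, borrowing the primary outcome's ICC of 0.02 and counting baseline as a measurement time. The loss from dichotomising lies between about 36% and 66% of the information for cuts from 50/50 to 90/10, if the score is roughly normal. The document gives no scale, SD or cut-point, so this range is illustrative.

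Mini-app use shares the pre/post wording problem in Table 2, but not the dichotomisation problem. Nothing here touches the primary analysis or the sample size. The point should be dealt with before analysis, as a matter of secondary-outcome specification.

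**What to change.** 1. Reconcile Table 2, the follow-up paragraph of Study measures and outcomes, and the Analysis section on one self-efficacy definition and one schedule.
2. Analyse the self-efficacy score as continuous in a linear mixed model with the same intervention and time terms as the primary model, adjusted for the baseline score. Keep any binary version as a supportive summary, with its cut fixed in advance.
3. Drop the pre-to-post rise as the analysed endpoint.
4. Use the quarterly schedule of Table 2 wherever the 3- and 9-month surveys can still carry the scale.
5. Analyse mini-app use as use in each quarter, as the Analysis section implies, in place of Table 2's pre/post comparison.

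The cost is SAP wording and some extra survey items at 3 and 9 months, possibly with an ethics amendment. The Trial status section says that recruitment has begun and analysis is pending, so some early surveys may already have passed. The change of definition and analysis is worth making even if the items cannot be added.
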